#### Inclusion procedure

The GP nurse will inform eligible patients about the online CDMIs and the study during a consultation. If the patient shows interest in participating, the GP nurse will hand over an envelope with: (1) an information brochure about the online CDMIs and (2) an information letter about the study. In addition, the GP nurse will send an invitation to the patient to participate in the online CDMIs by email (sent from the monitoring system). The patients will subsequently receive an email with information about the study and are asked if they are willing to participate in the study. If this is the case, they can click on a button which directs them to the informed consent form. They can then provide consent by clicking on the ‘I consent’ button. Following this, the patients are directed to a webpage where they can create their own online CDMI account by providing their email address, password and gender. After logging in to the online CDMIs for the first time they will be asked to complete the (online) baseline questionnaire. Data collected for research purposes will be stored in a database using a unique respondent number for each individual patient. Email addresses will be stored in a separate database on a separate server. Data will also be used for clinical purposes within the monitoring system. Data processing agreements will be put in place with the relevant parties, besides the research team, who have access to the data for this purpose (ICT parties/monitoring system provider and primary care organisations). Patients who indicate that they do not wish to participate in the study are offered the opportunity (by clicking on a link) to use the self-help version of the online CDMIs (without the GP nurse being able to monitor progress and provide guidance using a monitoring system). The flowchart of the study is presented in Fig. 1.

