### Aim

The aim of this study is to evaluate whether a SES-sensitive implementation strategy to implement the online CDMIs in primary care improves the percentage of lower-SES participants as compared to a regular implementation strategy. The hypothesis is that the percentage of lower-SES participants in the online CDMIs will be higher in the SES-sensitive implementation strategy group as compared to the regular implementation strategy group.

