### Design

A pragmatic cluster randomised controlled trial with two parallel groups will be conducted in which the two implementation strategies will be compared. As the GP nurse plays a key role in the implementation strategies, randomisation will take place at the level of the GP nurse in order to avoid contamination between the two implementation strategy conditions. Thus, each GP nurse will be randomised to one of the two implementation strategy groups. GP nurses cannot be blinded to the implementation strategy that they are allocated to because they will be aware whether their allocated implementation comprises specific components aimed at reaching lower-SES patients. The randomisation status will not be disclosed to patients. It is worth noting that the online CDMIs will be implemented in both conditions, meaning that the intervention will not be withheld from any patients participating in the study. Moreover, patients are free to receive any other type of care during the study. Participating patients will be assessed at baseline (T0), 3 months after baseline (T1) and 12 months after baseline (T2). Assessments among participating GP nurses will take place at two time points: at baseline, and 6 months after baseline. See Fig. 1 for the flowchart of the study and Table 1 for an overview of the schedule of enrolment, interventions and assessments in accordance with the SPIRIT Statement. This study is registered at the Netherlands Trial Register (NL6595) and was approved by the Medical Ethics Committee of the VU University Medical Center.

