##### SES-sensitive implementation strategy

The SES-sensitive implementation strategy will encompass all the topics described in the regular implementation strategy, but will be tailored to match the needs of the lower-SES target group.

The GP nurses will receive a 3-h training (instead of a 2-h training), and follow-up meeting of 1.5 h (approximately 2 months after the training visit) in which extra elements of the SES-sensitive implementation strategy will be addressed. This additional section of the training was developed in collaboration with a representative of the Dutch Centre of Expertise on Health Disparities (Pharos). An important component is the recognition and guidance of lower-SES patients who might benefit from the online CDMIs. GP nurses will be taught about the concept and consequences of health-literacy skills and ways to recognise and align with the needs of patients with a lower SES or low/limited health-literacy skills. They will practice with methods to provide support to patients with lower SES or health-literacy skills (e.g. easier language and communication, teach-back method). They will also be strongly advised to provide a more directive approach to guiding patients and encouraging them to use the CDMIs. Practical tips will be given to do this, such as: not immediately offering the online CDMIs during the first visit, but after trust and alliance have been established, seeking contact more often (face-to-face, by telephone or monitoring system) to provide guidance, helping patients create an account, indicating which exercises the patient should do (an overview of exercises and suggestions is given in the manual), doing the online exercises with patients during face-to-face sessions before doing them alone (modelling), focussing on one or a few exercises to reduce the chance of experiencing failure, using appropriate language and checking whether information is understood (e.g. using the teach-back method).

The GP nurses in this condition will also have access to a helpdesk service, at least two implementation team meetings and ongoing communication activities from the research teams, but special attention will be paid to the lower-SES target group in all these actions.

Additional elements of the SES-sensitive implementation strategy aimed at the patients are:

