▪ Extra guidance from the GP nurse, when needed, during the registration process (creating an account, username/password, intake questionnaire, etc.)▪ Extra guidance from the GP nurse, if necessary, with the exercises (e.g. the GP nurse and the patient practice the exercise together during a consultation)▪ A more proactive approach of delivering support by the GP nurse (e.g. extra reminders, extra contact moments by email or phone)

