### Outcome measures

#### Primary outcome

The (difference in the) participation rate of patients with a lower SES in the CDMIs is the primary outcome. Participation is defined as participating in at least one face-to-face session with a GP nurse (as registered by the GP nurse) and engaging with at least two exercises in the online CDMIs (as determined with the user data of the online CDMIs). It is hypothesised that in the SES-sensitive implementation strategy arm of the trial the participation rate of lower-SES patients will be significantly higher than in the regular implementation strategy arm. This outcome requires an operational definition of SES, but SES can be defined in various ways. Indicators that are commonly used are education, income and work status/occupation [31–35]. Education is a widely used indicator, especially in the Netherlands, and has some advantages over the other two indicators [36–38]. First, the level of education is generally stable after early adulthood, whereas work status and level of income fluctuate more. Second, in general, respondents are willing to report their level of education, while respondents might be unwilling to disclose or even misstate the level of their income [38, 39]. For these reasons, education will be the main indicator of lower SES in this study. In addition to education level, income, work status and status level of the neighbourhood will be taken into account because these indicators cover different dimensions of SES and are, although interrelated, not interchangeable with education [33, 34].

Therefore, in this study, a lower SES will be defined as:
The highest completed educational level is intermediate vocational education (i.e. between lower and higher vocational education, in Dutch: MBO in Dutch: MBO) or lower, and/orThe respondent is unemployed (looking for work) and lives in a neighbourhood with a negative status level score, and/or:The total gross family income of the respondent is below the social minimum income in the Netherlands (per July 2017), and lives in a neighbourhood with a negative status score

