### Statistical analysis

#### Primary outcome

The effect of the implementation strategies on lower-SES participation will be analysed using mixed-effects logistic regression models. This analysis technique allows for the clustering of patients within primary care practices, for dependence of observations within individuals over time, and provides intention-to-treat analysis as required by the Consolidated Standards of Reporting Trials (CONSORT) Statement. The allocated implementation strategy will be used as the fixed between-groups factor.

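### The primary participation rate is conditional on registration, a post-randomisation step that the SES-sensitive strategy is designed to change, and its denominator is not written out, so it cannot by itself show an effect on reach

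*Protocol article*

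**What the plan says.** All points are from the protocol article.

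- **Outcome.** Primary outcome (under Outcome measures): "The (difference in the) participation rate of patients with a lower SES in the CDMIs is the primary outcome". Participation means at least one face-to-face session and two online exercises. The Abstract treats this rate as reach. The Aim words it differently: the strategy "improves the percentage of lower-SES participants as compared to a regular implementation strategy". Neither section writes out a denominator.
- **When SES becomes known.** Education, income, work status and zip code are self-reported by respondents. Under Inclusion procedure the order is: information and interest, email invitation, consent, account creation, first login. Only then: "After logging in to the online CDMIs for the first time they will be asked to complete the (online) baseline questionnaire". No SES record is described for patients who stop earlier. Those who decline the study are directed to a self-help version that the nurse does not monitor.
- **Who recruits.** Under Design, "GP nurses cannot be blinded to the implementation strategy that they are allocated to". Under Eligibility criteria and recruitment, nurses recruit according to the strategy to which they were randomised.
- **What differs between arms before SES is recorded.** The SES-sensitive training covers recognising lower-SES patients. Its practical tips include "not immediately offering the online CDMIs during the first visit, but after trust and alliance have been established" and helping with account creation. Its patient-level elements include "Extra guidance from the GP nurse, when needed, during the registration process".
- **Analysis.** Statistical analysis, Primary outcome: a mixed-effects logistic model that "provides intention-to-treat analysis as required by the Consolidated Standards of Reporting Trials (CONSORT) Statement".

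**The concern.** The trial asks whether the strategy reaches more lower-SES patients. Reach has two parts: getting such patients to register, and getting those who register to participate. The described data capture only the second part for identifiable lower-SES patients, because someone who never logs in has no recorded SES. The first part is where one arm receives extra recognition and registration help.

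The patients in the analysis are thus selected after randomisation, by an arm-dependent process run by staff who know the allocation. Intention-to-treat protects a comparison when everyone randomised, or everyone belonging to a randomised cluster, is accounted for. A mixed model cannot restore eligible patients who were never recorded. At stake is the reading of the primary result: neither a null nor a positive patient-level comparison could be taken directly as an effect on reach.

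**Working it through.** **1. The plan's own figure.** Inputs (Sample size calculation): 18% vs 36%, two-sided 5%, 80% power, mean cluster size 6, range 2–14, ICC 0.02. The pooled-variance formula gives

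n = [1.96·√(2·0.27·0.73) + 0.8416·√(0.18·0.82 + 0.36·0.64)]² / 0.18² = 94.3, so 95 per arm.

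Design effect = 1 + ((1 + CV²)·6 − 1)·0.02. The CV of cluster size is not stated. Taking 0.577 (SD of an even spread over 2–14, 12/√12 = 3.46, divided by 6) gives 1.14. Then 95 × 1.14 = 108.3, or 19 nurses of 6 = 114 per arm, as stated. The sample-size arithmetic is not at fault; the question is what the 18% and 36% are percentages of.

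**2. Denominator = registered lower-SES patients.** The documents give no registration rates, so all inputs here are assumptions. Registration is 30% (regular) and 60% (SES-sensitive). Patients who would register under either strategy participate at 60%; the added registrants participate at rate a.

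- Regular: reach = 0.30 × 0.60 = 18%; analysed rate = 60%.
- SES-sensitive: reach = 0.30 × 0.60 + 0.30 × a; analysed rate = reach / 0.60.

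| a | Reach, regular → SES-sensitive | Analysed rate, regular → SES-sensitive |
|---|---|---|
| 20% | 18% → 24% | 60% → 40% |
| 40% | 18% → 30% | 60% → 50% |
| 60% | 18% → 36% | 60% → 60% |
| 80% | 18% → 42% | 60% → 70% |

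The planned doubling can therefore appear as no difference, and smaller real gains as losses. This does not require the strategy to be useless after registration. If it also raises the first group from 60% to 65% and a = 30%, reach is 0.30 × 0.65 + 0.30 × 0.30 = 28.5%, but the analysed rate is 28.5/60 = 47.5%.

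If 18% is instead the rate among registrants, with a = 10%, the analysed rate falls from 18% to (0.30 × 0.18 + 0.30 × 0.10)/0.60 = 14%, while reach rises from 5.4% to 8.4%.

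**3. Outcome = lower-SES share of participants.** Assume equal numbers of eligible lower- and higher-SES patients, and higher-SES reach of 35% in the regular arm. The share there is 18/(18 + 35) = 34.0%.

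- Only lower-SES reach rises, to 36%: 36/(36 + 35) = 50.7%. Right direction.
- Both rise by half: 27/(27 + 52.5) = 34.0%. Flat, although lower-SES reach rose 9 points.
- Lower-SES to 24%, higher-SES to 60%: 24/(24 + 60) = 28.6%. A fall, although lower-SES reach rose 6 points.

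**4. Power of a nurse-level count.** If 18% and 36% apply to 114 patients per arm, expected counts are 20.5 and 41.0 over 19 nurses each. Var(log rate ratio) = 1/20.5 + 1/41.0 + 2·CV²/19, where CV² is the between-nurse variation (assumed). Power = Φ(0.693/SE − 1.96).

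- CV² = 0: SE 0.270, power about 73%.
- CV² = 0.25: SE 0.315, power about 59%.
- CV² = 0.5: SE 0.355, power about 50%.

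**The case against.** **The denominator is not stated, and part of the text points away from registered lower-SES patients.** The Aim speaks of a percentage of lower-SES participants. Additional analyses treats lower SES as an outcome, and Sociodemographic factors says data are needed from all patients. On a share reading, bringing lower-SES patients into registration is part of the effect being measured. With 100 eligible patients per SES group per arm and 50 higher-SES registrants per arm (assumed), the lower-SES share of everyone enrolled goes from 30/80 = 37.5% to 60/110 = 54.5%. This stands: reversal is not inherent in the outcome. It does not remove the problem, because a share is also formed after randomisation and responds to higher-SES uptake. A hybrid, lower-SES participants over all enrolled, can go either way: 18/80 = 22.5% becomes 30/110 = 27.3% at a = 40%, but 24/110 = 21.8% at a = 20%.

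**Some material is unseen.** The flowchart and schedule are not shown, and no sentence places the SES items in the baseline questionnaire. That placement is an inference, though a well-supported one. A fuller document could state the denominator. An analysis plan alone could not supply SES for patients from whom it was never collected.

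**Unblinded, arm-dependent recruitment is disclosed and natural in a pragmatic implementation trial.** Agreed. The objection is to calling the patient-level result intention-to-treat for reach, not to the design.

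**Stronger readings that the documents do not support.** A reader might infer that nurses who recruit nobody will be dropped. The range 2–14 is only a sample-size input, and no exclusion rule is stated, although such a nurse contributes no rows to a patient-level model. A reader might also infer that the later offer is more selective; the text advises on timing and does not say that fewer patients are offered the intervention.

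**Conclusion.** The concern holds in a limited form. SES is apparently recorded only after registration, recruitment is unblinded and follows allocation, and the SES-sensitive strategy acts on recognition, offer and registration. The primary rate is therefore conditional on a step that the strategy is designed to change, and the intention-to-treat statement does not hold for reach.

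The size depends on which denominator is meant. Among registered lower-SES patients, and under the assumed 30% vs 60% registration, true reach of 24% to 42% (against 18%) corresponds to an analysed rate of 40% to 70% (against 60%). As a share of participants, the measure behaves properly if only lower-SES reach rises and fails only if higher-SES uptake rises as well.

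It would go too far to conclude that the trial will miss or reverse a real gain. The registration rates are assumed, and the documents determine neither direction nor size.

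**What to change.** 1. State the denominator of the participation rate identically in Aim, Primary outcome and Statistical analysis, and say to which denominator the 18% and 36% refer.
2. Label the mixed-effects logistic result as conditional on registration, and remove the claim that it is intention-to-treat for reach.
3. Pre-specify a key supportive analysis: number of lower-SES participants per randomised GP nurse, with nurses who recruit nobody counted as zero. Use negative binomial regression, or Poisson with robust standard errors, with an offset for recruitment months (and practice list size or consultations where available), adjusted for the neighbourhood-SES stratum. This needs SES only for patients who participate, all of whom have logged in.
4. Limit any conclusion about reach to what that analysis supports.
5. Report invitation counts by arm descriptively only. They come after randomisation and after the patient has shown interest, so they do not give a neutral denominator.

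**Cost.** Recruitment months and, where available, exposure data per nurse; one further model; and changes of wording. The offset is approximate because nurses differ in workload and patient mix. Power is about 73% at best and about 50% to 59% under the overdispersion assumed above, so the analysis should be read by its estimate and interval and not by significance alone. Resting the whole claim on it as a sole primary test would be a poor trade at this sample size.

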#### Monitoring system

To facilitate the implementation of the blended CDMI format in primary care, the online CDMIs will be linked to a monitoring system allowing the GP nurses to check on the patient’s progress when using the CDMIs and to track complaints over time. The monitoring system will provide the GP nurse with insight into the intervention use of their patients (e.g. answer to questionnaires, diary entries, number of logins, number of completed exercises), and allows them to send messages to their patients.

#### Implementation strategies

Successful implementation of e-health is not only related to the patient-related factors, but also to the intentions and motivations of health care providers and their management [28, 29]. This means that GP nurses play a crucial role in the implementation process. In this study, the main focus of the implementation strategies is aimed at the GP nurses and the patients. That being said, management-level representatives of the two participating organisations will be actively involved during the implementation process and will also be members of an Advisory Committee that will be installed for the purpose of this project. This will allow for an ongoing dialogue about relevant organisational aspects and possibilities for (organisational) support or even change throughout the implementation process. The main aim of the Advisory Committee is to advise the project team on a range of content- and implementation-related issues in order to facilitate the execution of the project. Their role is thus advisory: their suggestions will be carefully considered, yet they do not have decision-making power. Besides the representatives of the participating organisations, members of the Advisory Committee will be independent of the trial. Given the goal of our project to compare two implementation strategies for the online CDMIs (an intervention that has been studied in a previous trial), and the implementation-related primary outcome of this study, we did not install a data monitoring committee. A DMC was also not part of the approved protocol.

The implementation strategy development process was informed by the implementation model of Grol & Wensing [30]. Before developing and selecting specific implementation strategies, this model suggests: (1) developing a proposal for change (in this study the adapted blended CDMIs), (2) an analysis of actual performance and targets for change and (3) a problem analysis including characteristics of the target group, the setting, and possible barriers and facilitators for implementation. With respect to step 2, as noted above, the uptake of e-health interventions leaves a lot to be desired, especially in lower-SES populations. Therefore, increasing the participation rates of people with a lower educational level is the main target for change in this study (see sections ‘Primary outcome’, and ‘Sample size’ calculation for more details). For the problem analysis, interviews and focus group meetings were conducted with people with a low-SES background, people with (a former) depression, GP nurses and other professionals working with people with mental health problems or a low SES, and this was supplemented with findings from the literature. Results from the problem analysis were also used for adapting the actual CDMIs courses for use in primary care.

Based on the findings of the previous three steps, we developed and selected sub-strategies (step 4) to create the overall regular implementation strategy and the SES-sensitive implementation strategy. As can be discerned from the description of the regular and the SES-sensitive implementation strategies outlined below, the same general (sub-)strategies are applied in both implementation strategies, but some are tailored to be SES-sensitive in the SES-sensitive implementation strategy. The implementation strategies will be evaluated in step 5 using the RCT described in this protocol. The model also suggests a continuous evaluation of the implementation process, and adapting it if necessary.

##### Regular implementation strategy

Prior to the start of the study, the research team will visit the implementation locations and give a presentation during GP nurse team meetings to garner interest in, and support for, the study.

Participating GP nurses who have been randomised to the regular implementation strategy will then be invited to attend a 2-h training in which they will:
▪ Learn about the online CDMIs, the related monitoring system and guidelines for the recruitment and guidance process▪ Practice using the online CDMIs and its monitoring system▪ Discuss possible barriers and facilitators for implementation

To be able to tailor the guidance to specific individual needs of patients, GP nurses in the control condition will be free in the amount of guidance they give. The only requirement is that they provide at least one face-to-face consultation. However, the basic advice suggested in the implementation manual is to schedule 3 consultations: at the start, midway and at the end of the period in which the CDMIs are used by the patient. It is also up to the GP nurses whether or not to recommend certain modules or exercises within the CDMIs. During the training general guidelines for topics that can be discussed during the consultations (e.g. what kind of instruction to give about the online CDMIs, discussing the diary, giving compliments) as well as indicating potential (motivational) barriers of patients to initiate and maintain usage of the online CDMIs. The GP nurses will be provided with a manual with information on all the topics covered during the training. After a practice period of approximately 2 months, the GP nurses will be invited to participate in a follow-up session, led by the research team, to exchange experiences and discuss potential problems that arose during the practice period.

The research team will provide ongoing support to the GP nurses throughout the implementation period in several ways:
▪ A helpdesk service (email or telephone contact) will be provided to support GP nurses to handle technical and implementation-related issues▪ At least two implementation team meetings (led by the research team) will be organised in which the participating GP nurses will be able to exchange their experiences, tips, ideas and to discuss encountered implementation barriers with each other. These meetings will also provide the research team with the opportunity to provide additional information, make adjustments or reiterate important issues if necessary▪ Regular communication from the research team with the GP nurses through newsletters, telephone calls and emails to keep the online CDMIs on the agenda of the GP nurses, and provide ongoing information and tips

The main elements of the regular implementation strategy aimed at the patients are: (1) a brochure with information about the online CDMIs, information about privacy, the study, and required time investment, (2) providing reminders to use the online CDMIs after a lack of activity and (3) receiving support from the GP nurse according to the guidelines for the GP nurse as outlined the CDMI implementation manual.

More information about the regular implementation strategy is provided in Table 2 below.

**Table 2 Tab2:** Detailed overview of the regular implementation strategy

Adaptation of the online Complaint-Directed Mini-Interventions (CDMIs) to allow use by general practice (GP) nurses in a blended format	
• Developing a monitoring system that allows GP nurses to: ◦ Invite patients to create an account ◦ Monitor use of CDMIs ◦ Track mood and complaints ◦ Provide the opportunity to message patients	
Create awareness of CDMIs and implementation project among GPs and GP nurses	
• Providing an information brochure for GPs to facilitate patient flow to the GP nurse and online CDMIs • Short outreach presentation during team meetings to teach/inform GP nurses about the CDMIs (including an information sheet and test-account)	
Provide training to GP nurses in using the CDMIs and guiding patients	
• Two visits: a training of *2* h and a follow-up meeting of *1* h (approximately 2 months after the training visit). The goals of the visits are to target: ◦ Knowledge about the CDMIs, the recruitment and guiding process, skills to use the intervention, creating self-efficacy and a positive attitude, motivation, intentions to use the CDMIs ◦ Training topics: 1. Providing information about the CDMIs, the related monitoring system and guidelines for the recruitment and guidance process 2. Practising with the use of the CDMIs and monitoring system 3. Discussing possible barriers and facilitators for implementation • With respect to guidance, flexible guidelines were given to promote maximum adaptability to local needs and procedures of GP nurses. Guidelines include:Highlighting the benefits of the CDMIs with guidance, explaining the content and goal of the intervention, discuss the desirable frequency and content of guidance sessions (suggestions for topics are given in the manual), examples of motivational interviewing techniques, monitor and discuss progress in an interim evaluation, final evaluation of the intervention (process) • The follow-up meeting is aimed at: discussing first experiences, barriers and facilitators, repeating the main elements of the way recruitment and guidance is being given.	
Create and provide educational materials to GP nurses	
• Developing manuals, and other supporting materials (PowerPoint presentation, flowchart) in ways that make it easier for GP nurses to learn about the CDMIs and for GP nurses to learn how to deliver the CDMIs to patients. The educational materials contain information on: The usefulness of blended e-health, the content of the CDMIs, the monitoring system, steps and guidelines to be taken in the recruitment and guidance process (including motivational interviewing techniques), the study flowchart and patient information	
Facilitate exchange of information and experiences among GP nurses	
• Organising at least two implementation team meetings per participating organisation during the year following the training and follow-up visits (led by the research teams). The participating GP nurses will be given time to reflect upon and share their experiences, share lessons learned and support each other’s learning. Moreover, the research team can provide additional information, support or solve problems as needed. The aim is to contribute to increasing motivation, self-efficacy, and intentions to use the CDMIs and to remove potential barriers for implementation	
Facilitate a process of interactive problem solving and support for GP nurses	
• Providing a helpdesk (by telephone or email) for the GP nurses for either technical questions or questions about the implementation process, and actively providing information and tips to GP nurses through newsletters, telephone calls and emails. The aim is to contribute to increasing motivation, self-efficacy and intentions to use the CDMIs and to remove potential barriers for implementation	
Create awareness among patients about the CDMIs and the implementation project	
• Providing an information brochure and letter for patients to inform them about the online CDMIs and the research study	
Facilitate and encourage the use of the CDMIs among patients	
• Making adjustments to CDMIs to make them user friendly (e.g. providing reminders for use, simplifying some of the navigation and texts) • Providing additional information about the CDMIs and offering the opportunity to ask questions during the GP nurse consultation • The GP nurse can also show a demo video in which the content and goal of the online CDMIs are explained.	
Motivate and provide support to patients when using the online CDMIs	
• Providing guidance at each step during the intervention, if necessary. The aim is to teach the necessary skills to use the intervention, and create a positive attitude and motivate patients to use the CDMIs. • Guidance is provided according to the regular implementation strategy guidelines described above	

